| Technical Summary (Max. 300 words) The aim of this study is to estimate the relative risk of anxiety and depression (primary outcomes), and fatigue, pain, sleep disorders, neurocognitive and sexual dysfunctions, and fatal and non-fatal self-harm (secondary outcomes), in breast cancer survivors compared to non-cancer controls. This study will be a matched cohort study, utilising data from the CPRD GOLD primary care database. Outcome-specific algorithms will be developed and validated to identify outcomes in the data. Algorithm development will consider Read codes for diagnoses, prescriptions, referrals and symptoms; prevalence and incidence estimates by age-group and sex will be computed for a random sample of patients selected from CPRD GOLD primary care database. Validation will be against external sources of data, namely published data from population-based surveys in the UK. To estimate the associations between breast cancer survivorship and the primary and secondary outcomes, we will identify all women exposed to breast cancer in the CPRD GOLD primary care database, and randomly select an age- and primary-care-practice-matched cohort of women without prior cancer in a ratio of 1:4. Cox regression models will be used to estimate hazard ratios adjusted for important confounders, and to explore the role of effect modifiers; the proportionality of hazards will be tested graphically and inferentially. |
| Outcomes to be Measured  - Anxiety - Depression - Fatigue - Cognitive impairment - Pain - Sexual dysfunction - Sleep disorders - Completed suicide - Self-harm |

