| Study Design The research aims will be addressed with a matched cohort study design.  Two cohorts will be assembled from the CPRD GOLD primary care database:  (1) The exposed cohort will include women diagnosed with a breast cancer (list of Read codes available in appendix 2) after at least 12 months of uninterrupted up-to-standard follow-up in CPRD (to ensure that the breast cancer is an incident event).  (2) A comparison cohort will be assembled by randomly selecting, for each woman with a breast cancer diagnosis, up to 4 women of similar age (3-year range), attending the same GP practice and with at least 12 months of uninterrupted up-to-standard data quality for research, but with no history of cancer at the date of the breast cancer diagnosis of the matched breast cancer patient.  The index date will be the date of breast cancer diagnosis for the exposed group; comparison patients will take the same index date as their exposed match. Please see section L for more details.  Inclusion criteria for both cohorts are: female sex, aged ≥18 years, and having a clinical record with at least 12 months of uninterrupted up-to-standard data quality for research (as measured by CPRD) before the breast cancer diagnosis date (to ensure the cancer record represents incident disease). Exclusions will be the diagnosis of severe mental illness (i.e. organic mental disorder, mental disorders due to substances, schizophrenia, delusional disorders, or manic or bipolar episodes), having a history of the specified mental health outcome in the year before index date; and having had a diagnosis of any other cancer prior to the index date.  All women will be followed from the index date until the earliest date of: outcome observed, a cancer diagnosis, death recorded, transference out of the practice; last data collection for the practice.  Matching will allow close control of key covariates, include GP practice that is difficult to adjust for in a statistical model (too many levels), and has the practical advantage of reducing the size of the comparison group (which might otherwise include several million women) by restricting to the most relevant comparison patients. |

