| Sample size considerations Table 2 shows the minimum relative risk that could be detected with the 52,335 women identified in the CPRD GOLD primary care database, for different probabilities of type I (α) and type II error (β). These estimates were obtained with the command ‘power’ in Stata v15 [15].  Table 2 Minimum RR that can be detected with the 52,355 women with a history of breast cancer and 209,420 women who did not have cancer, for different probabilities of type I and type II errors, and baseline risk of the outcomes.   \| **Outcome** \| **α** \| **β** \| **% of outcome in unexposed group [ref]** \| **Min. HR possible to be estimated** \| \| **RR/HR estimated in other studies [ref]** \| \| \| --- \| --- \| --- \| --- \| --- \| --- \| --- \| --- \| \|  \|  \|  \|  \|  \| \|  \| \| \| **Primary outcomes** \|  \|  \|  \|  \| \|  \| \| \|  \|  \|  \|  \|  \| \|  \| \| \| **Anxiety, diagnoses** \| **0.05** \| **0.20** \| **5 [7]** \| **1.05** \| \| 1.06 [7]  1.08 [7]  1.22 [11]  1.25 [8] \| \| \| **0.01** \| **0.20** \| **5 [7]** \| **1.06** \| \| \| **0.05** \| **0.10** \| **5 [7]** \| **1.06** \| \| \| 0.01 \| 0.10 \| 5 [7] \| 1.07 \| \| \|  \|  \|  \|  \| \| \| **0.05** \| **0.20** \| **20 [11]** \| **1.02** \| \| \| **0.01** \| **0.20** \| **20 [11]** \| **1.03** \| \| \| **0.05** \| **0.10** \| **20 [11]** \| **1.03** \| \| \| **0.01** \| **0.10** \| **20 [11]** \| **1.03** \| \| \|  \|  \|  \|  \|  \| \|  \| \| \| **Anxiety, prescription of**  **anxiolytics** \| **0.05** \| **0.20** \| **3 [10]** \| **1.07** \| \| 1.08 [7]  2.52 [10] \| \| \| **0.01** \| **0.20** \| **3 [10]** \| **1.08** \| \| \| **0.05** \| **0.10** \| **3 [10]** \| **1.08** \| \| \| 0.01 \| 0.10 \| 3 [10] \| 1.09 \| \| \|  \|  \|  \|  \| \| \| **0.05** \| **0.20** \| **8 [7]** \| **1.04** \| \| \| **0.01** \| **0.20** \| **8 [7]** \| **1.05** \| \| \| **0.05** \| **0.10** \| **8 [7]** \| **1.05** \| \| \| **0.01** \| **0.10** \| **8 [7]** \| **1.06** \| \| \|  \|  \|  \|  \|  \| \|  \| \| \| **Depression, diagnoses** \| 0.05 \| 0.20 \| 3 [11] \| 1.07 \| \| 1.06 [7]  1.39 [9]  1.49 [8]  1.94 [11] \| \| \| 0.01 \| 0.20 \| 3 [11] \| 1.08 \| \| \| 0.05 \| 0.10 \| 3 [11] \| 1.08 \| \| \| 0.01 \| 0.10 \| 3 [11] \| 1.09 \| \| \|  \|  \|  \|  \| \| \| **0.05** \| **0.20** \| **9 [7]** \| **1.04** \| \| \| **0.01** \| **0.20** \| **9 [7]** \| **1.05** \| \| \| **0.05** \| **0.10** \| **9 [7]** \| **1.04** \| \| \| **0.01** \| **0.10** \| **9 [7]** \| **1.05** \| \| \|  \|  \|  \|  \|  \| \|  \| \| \| **Depression, prescription of**  **antidepressants** \| **0.05** \| **0.20** \| **2 [10]** \| **1.08** \| \| 1.16 [7]  1.95 [10] \| \| \| **0.01** \| **0.20** \| **2 [10]** \| **1.10** \| \| \| **0.05** \| **0.10** \| **2 [10]** \| **1.09** \| \| \| **0.01** \| **0.10** \| **2 [10]** \| **1.11** \| \| \|  \|  \|  \|  \| \| \| **0.05** \| **0.20** \| **20 [7]** \| **1.02** \| \| \| **0.01** \| **0.20** \| **20 [7]** \| **1.03** \| \| \| **0.05** \| **0.10** \| **20 [7]** \| **1.03** \| \| \| **0.01** \| **0.10** \| **20 [7]** \| **1.03** \| \| \|  \|  \|  \|  \|  \| \|  \| \| \| **Secondary outcomes *** \|  \|  \|  \|  \| \|  \| \| \|  \|  \|  \|  \|  \| \|  \| \| \| **Sexual dysfunction** \| 0.05 \| 0.20 \| 4.1 [16] \| 1.06 \| \| 1.03 [16]  2.27 [17] \| \| \| 0.01 \| 0.20 \| 4.1 [16] \| 1.07 \| \| \| 0.05 \| 0.10 \| 4.1 [16] \| 1.07 \| \| \| 0.01 \| 0.10 \| 4.1 [16] \| 1.08 \| \| \|  \|  \|  \|  \| \| \| 0.05 \| 0.20 \| 9.1 [17] \| 1.04 \| \| \| 0.01 \| 0.20 \| 9.1 [17] \| 1.05 \| \| \| 0.05 \| 0.10 \| 9.1 [17] \| 1.04 \| \| \| 0.01 \| 0.10 \| 9.1 [17] \| 1.05 \| \| \|  \|  \|  \|  \|  \| \|  \| \| \| **Suicide** \| 0.05 \| 0.20 \| 0.0008** [18] \| 1.47 \| \| 1.37 [18]  1.6 [19] \| \| \| 0.01 \| 0.20 \| 0.0008** [18] \| 1.60 \| \| \| 0.05 \| 0.10 \| 0.0008** [18] \| 1.57 \| \| \| 0.01 \| 0.10 \| 0.0008** [18] \| 1.70 \| \| \|  \|  \|  \|  \|  \| \|  \| \| \| **Fatal and**  **non-fatal self-harm** \| 0.05 \| 0.20 \| 0.005 [18, 20] \| 1.17 \| \| 1.03 [21]  1.37 [18] \| \| \| 0.01 \| 0.20 \| 0.005 [18, 20] \| 1.21 \| \| \| 0.05 \| 0.10 \| 0.005 [18, 20] \| 1.20 \| \| \| 0.01 \| 0.10 \| 0.005 [18, 20] \| 1.24 \| \| \|  \|  \|  \|  \|  \| \|  \| \| \| **Sleep disturbances** \| 0.05 \| 0.20 \| 50 [22] \| 1.01 \| \| 0.8 [22] \| \| \| 0.01 \| 0.20 \| 50 [22] \| 1.02 \| \| \| 0.05 \| 0.10 \| 50 [22] \| 1.02 \| \| \| 0.01 \| 0.10 \| 50 [22] \| 1.02 \| \| \|  \|  \|  \|  \|  \| \|  \| \| \| **Prescription of hypnotics** \| **0.05** \| **0.20** \| **4 [23]** \| **1.06** \| \| 3.75 [23] \| \| \| **0.01** \| **0.20** \| **4 [23]** \| **1.07** \| \| \| **0.05** \| **0.10** \| **4 [23]** \| **1.07** \| \| \| **0.01** \| **0.10** \| **4 [23]** \| **1.08** \| \| \|  \|  \|  \|  \|  \| \|  \| \| \| **Mild cognitive impairment** \| **0.05** \| **0.20** \| **5 [24]** \| **1.05** \| \| 1.58 [25]  1.60 [26]  2.43 [24]  3.67 [27] \| \| \| **0.01** \| **0.20** \| **5 [24]** \| **1.06** \| \| \| **0.05** \| **0.10** \| **5 [24]** \| **1.06** \| \| \| **0.01** \| **0.10** \| **5 [24]** \| **1.07** \| \| \|  \|  \|  \|  \| \| \| **0.05** \| **0.20** \| **19 [26]** \| **1.02** \| \| \| **0.01** \| **0.20** \| **19 [26]** \| **1.03** \| \| \| **0.05** \| **0.10** \| **19 [26]** \| **1.03** \| \| \| **0.01** \| **0.10** \| **19 [26]** \| **1.04** \| \| \|  \|  \|  \|  \| \|  \| \|  \| \|   HR – hazard ratio. RR – risk ratio. Bold is used to denote where the minimum risk ratio that could be detected with the available sample size is lower than the lowest estimate reported in the literature.  * No population-based studies have been identified reporting the relative risk of sexual dysfunctions, pain, fatigue, sleep disorders or cognitive dysfunction in breast cancer survivors compared to the non-cancer female population. Thus, the relative risk reported in the column for the other studies comes from studies involving convenience samples of cancer survivors. Pain and fatigue are often evaluated using psychometric instruments whose mean scores are summarised as means for between-group comparisons; no studies were identified providing data for the prevalence of pain and fatigue in breast cancer survivors and in women who did not have cancer, and thus these two outcomes were not included in the table.  ** Calculated as the proportion of suicides in the exposed group divided by the inverse of the standardised mortality ratio reported in the original study.  The available sample size is expected to be sufficient for detecting clinically significant increases of anxiety and depression (primary outcomes) in breast cancer survivors compared to the women who did not have cancer.  For the secondary outcomes, sample size is likely to be enough to assess differences in sleep disturbance measured by hypnotics’ prescription, and mild cognitive impairment. However, the available sample size will have relatively small power to detect small differences in suicide between women with history of breast cancer and those who did not have cancer, because this is a rare outcome, but we will still have enough power to detect associations of a magnitude seen in some previous studies; data from our analysis can also contribute to future meta-analyses. |

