| Data/ Statistical AnalysisPrimary analysesSpecific aim 1. To develop and validate algorithms to identify patients with anxiety and depression Algorithm development  A systematic review is currently under way to identify the lists of Read codes previously used to define anxiety and depression of primary care databases in the UK. The systematic review search expressions are provided in appendix 5.  *(A) Raw data tabulations*  We will estimate the number and proportion of patients recorded during the observation period with:   1. Diagnostic Read code for anxiety/depression; 2. Prescription of anxiolytics/antidepressants; 3. Referred to mental health services; 4. Symptoms of anxiety/depression.   Proportions will be estimated by calendar year.  *(B) Simpler algorithm*  We will estimate the additional contribution of prescriptions, referrals and symptoms to identify cases of anxiety/depression in CPRD. Referrals and prescriptions of anxiolytics/antidepressants will be considered as sufficient to identify cases of anxiety/depression if a Read code for symptoms of anxiety/depression, respectively, were recorded during the previous year. The reasons for this are threefold: (1) there is good evidence that GPs switched from anxiety/depression diagnostic codes to symptomatic ones [44, 45], following claims of over diagnosis of these conditions; (2) antidepressants and anxiolytics have also other indications, including anxiety disorders for antidepressants [46], which raise questions of the use of these data their own to identify these outcomes; (3) pharmacological treatment of mild depression has been discouraged since 2004 [47], and thus referrals to psychotherapy may help to capture milder cases.  *(C) Complex algorithm*  A more detailed algorithm will be developed considering that some drugs are prescribed for both depression and anxiety, in addition to manage vasomotor symptoms, which may be more frequent in breast cancer survivors than in women who did not have cancer. An example for depression is given in appendix 6. We will estimate the number of patients with anxiety/depression at each step, to evaluate how much each category adds to what has been previously recorded.  Algorithm validation  A random sample of 1 million patients of both sexes will be selected from the CPRD GOLD primary care database. We will apply each algorithm and produce descriptive statistics stratified by likelihood of having the outcome, including:   - Number and proportion of patients with the anxiety, depression or both, by 3-year calendar period; - Number and proportion of patients with the anxiety, depression or both, by 3-year calendar period, age and sex; - Number and proportion of patients with the anxiety and depression by 3-year calendar period and country in the UK.   For each outcome, we will compare the estimates obtained with others obtained from the literature, prioritising national surveys of population-based data such as the following:   - Adult Psychiatric Morbidity Survey 2007 [48] and 2014 [49]; - Measuring National Well-being programme, made available by the Office for National Statistics (includes prevalence of those in the UK with some evidence indicating depression or anxiety, since 2013, by country in the UK and English regions, and by 10-year age groups up to 75 years) [50].   The final algorithm will be chosen by considering information in the numeric value closer to the estimates obtained from the literature. Sensitivity analysis Proportion estimates considering the presence of symptomatic codes within the previous year will be re-calculated to consider shorter periods of time (i.e. 3 and 6 months). Specific aim 2. Risk of mental health outcomes in women who had breast cancer compared to women who did not have cancer**Primary outcomes analysis – depression and anxiety**Main analysis Descriptive statistics including number of events observed and person-years at risk will be computed, overall and stratified by the covariates listed in section M (see above). Medical procedures for the diagnosis of breast cancer are likely to cause anxiety. To deal with this we planned to exclude patients who had a record of anxiety diagnosed within 1 year before the breast cancer; this could result in patients with higher levels of trait anxiety being excluded from the analysis. We will calculate the number and proportion of patients who were excluded because they had the outcome in the year prior to the breast cancer, stratified by month. We will also describe how many of those who were excluded from analysis had an outcome after the breast cancer diagnosis by age-group. The quintiles of the distribution of the number of consultations (defined using the ‘consid’ variable) will be described, as this can indicate the patterns of seeking care between women with a history of cancer, compared to those who did not.  The association between breast cancer history and anxiety and breast cancer history and depression, will be quantified using Cox regression models with time since index as the underlying time scale, and stratifying on matched set to account for matching by age and primary care practice. Follow up will begin at the index date (vide section M for definition of the exposure) and will terminate when an outcome is observed. Women will be censored at the earliest date of any of these: cancer recurrence, other cancer diagnosis, death, transference out of the practice; if these events don’t occur, censoring will be observed at the date of last data collection for the practice. Crude measures of the association between breast cancer history and anxiety and depression will be reported stratifying by the covariates described in section M.  Cox multivariate regression analysis will be use to estimate hazard ratios adjusted for calendar period of breast cancer diagnosis, menopausal status, and diabetes mellitus at baseline (see list of confounders in section L, covariates, for the definition of these variables).  Interaction terms between the exposure and the following variables will be added, to explore effect modification by ethnicity (White, South Asian, Black, Others and mixed), place of residence (care home vs. household), co-habitation status (living alone vs. cohabiting), SES (quintiles of IMD), having mental health disorders history (yes vs. no), having history of stroke (yes vs. no) and coronary heart disease (yes vs. no).  Confidence intervals will be calculated using robust estimates of the standard errors, to account for the fact that patients may also contribute with time at risk in the unexposed cohort prior to their cancer diagnosis.  The proportional hazards assumption will be tested in two ways: 1) graphically, by plotting the cumulative rates on a log scale; 2) inferentially, by applying a likelihood ratio test to the estimates obtained for the entire period of observation and for time split into intervals. Sensitivity analyses Sensitivity analyses planned for this study will include a subset of patients only; this is because they use variables from linked data, which is available for a fraction of the patients only, and include variables amenable to have missing data (i.e. BMI, alcohol intake, smoking and patient-level IMD). Regarding the latter, we will quantify the completeness of each variable to decide on their inclusion in the final models. Analyses including variables with missing data will be restricted to patients with complete data for covariates (complete case analysis), if missing data is likely to be missing not a random. The following sensitivity analyses are planned:   1. The main analysis will be repeated further adjusting for age at diagnosis (continuous variable, since matching allowed for 3-year gap), patient quintile level of IMD, alcohol drinking patterns prior to index date, smoking history and body mass index categories prior to index date. 2. We will exclude women diagnosed with the outcome of interest in the year prior to the cancer diagnosis. To account for the fact that treatment for these conditions may often last for more than one year, and that mild anxiety and depression may be treated in psychological services and not result in visits to the GP, we will repeated the main analysis including only patients who had 5 years of complete follow up prior to the index date and did not have the outcome recorded at any point during this period.  Multiple comparisons We acknowledge that this study includes multiple comparisons for each outcome, and several outcomes. Thus, P-values in the range ~0.01-0.05 be considered as some statistical evidence of an effect and interpreted cautiously. Sample size considerations considering a 0.01 probability of type I error (α) are provided in see section I. Specific aim 3. To estimate association between breast cancer history and anxiety/depression by presence of lymphoedema, pain, mild cognitive impairment, fatigue, sexual dysfunction, sleep disorders, and having done endocrine therapy, during the follow up period. We will estimate the cumulative incidence and period prevalence of lymphoedema, pain, mild cognitive impairment, fatigue, sexual dysfunction, and sleep disorders, in breast cancer survivors during the overall follow up period and by 5-year of follow up period.  We will estimate the hazards of developing anxiety and depression (the main outcomes) for three groups of patients: 1) breast cancer survivors who did not develop the common complication (i.e. lymphoedema, pain, mild cognitive impairment, fatigue, sexual dysfunction, sleep disorders) up to time *t*; 2) breast cancer survivors who have had the common complication at time *t*; 3) women who never had cancer. A Cox regression model will be used to estimate the association between time-updated exposure and the main outcomes (anxiety and depression), having as reference the hazard observed for the women who did not have cancer. The exposure variable will be time-updated; this means that women who develop a common complication will contribute with information to group 1 until the date at which they develop the complication of interest; after this point they will contribute with information to group 2. All models will be adjusted for calendar period of breast cancer diagnosis.  Confidence intervals will be calculated using robust estimates of the standard errors. Sensitivity analyses planned in objective 2 will be applied to this objective as well. Secondary outcomes analyses – fatigue, mild cognitive impairment, pain, sleep disturbance, sexual dysfunction, fatal and non-fatal self-harm The steps outlined above will be repeated for the secondary outcomes. Sensitivity analysis will follow the same rationale as described for the primary analysis. |

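### Table 2 counts every expected event as informative, but the main Cox model is stratified on matched set; this is a second, smaller power shortfall on top of the equal-allocation variance behind the table

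*Protocol*

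**What the plan says.** Sample size considerations presents Table 2 as the "Minimum RR that can be detected with the 52,355 women with a history of breast cancer and 209,420 women who did not have cancer". The inputs are head counts, α, β and a baseline percentage. Matching, stratification, length of follow-up and loss from follow-up do not enter. A cell is bold when its minimum HR lies below the lowest published estimate, and the section concludes that the sample suffices for increases of clinical importance in anxiety and depression.

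The Technical Summary fixes the design as an "age- and primary-care-practice-matched cohort of women without prior cancer in a ratio of 1:4". Data/Statistical Analysis, Specific aim 2, Main analysis, fits a Cox model on time since index, "stratifying on matched set to account for matching by age and primary care practice".

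Study Design ends follow-up at the earliest of "outcome observed, a cancer diagnosis, death recorded, transference out of the practice; last data collection for the practice". The Main analysis adds recurrence: "Women will be censored at the earliest date of any of these: cancer recurrence, other cancer diagnosis, death, transference out of the practice". Otherwise, "censoring will be observed at the date of last data collection for the practice". No transfer, death or recurrence rate is given, and no mean follow-up.

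**The concern.** With one stratum per matched set, each event is compared only with the women of that set still at risk. Once the index case has gone, through her own outcome, death, cancer or transfer, every later risk set in that stratum is entirely unexposed, and those events drop out of the partial likelihood for the exposure HR. Comparison women supply about 80% of events near HR = 1, so the loss falls on the larger part of the data.

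Table 2 therefore states power and minimum HRs for an analysis other than the one written. What is at stake is the accuracy of the printed minimum HRs, the bold marking, and how far the sufficiency sentence reaches for the smallest published effects (1.06 and 1.08 for anxiety diagnoses, 1.06 for depression diagnoses).

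**Working it through.** **1. Reproduce Table 2.** Inputs: N = 52,355 + 209,420 = 261,775 (the text says 52,335 exposed; the difference changes no rounded cell); baseline risk, α and β from the table. Sidedness is not stated; two-sided reproduces the figures.

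HR = exp[(z₁₋α/₂ + z₁₋β) / √(D·v)], with D = N × risk and v = q(1−q), where q is the exposed share.

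Anxiety diagnoses, 5%: D = 261,775 × 0.05 = 13,089.
- v = 0.25 (equal allocation): 1.0502, 1.0616, 1.0583, 1.0698. Printed: 1.05, 1.06, 1.06, 1.07.
- v = 0.2 × 0.8 = 0.16 (1:4): 1.063, 1.078, 1.073, 1.088. These do not match.

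Over the whole table, v = 0.25 with all events counted matches 60 of 64 cells; the other four differ by 0.01.

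**2. The larger shortfall.** Power at HR 1.05, 5% risk, α 0.05 is Φ(ln 1.05 × √(D·v) − 1.96).
- v = 0.25: Φ(0.0488 × 57.2 − 1.96) = 80%.
- v = 0.16: Φ(0.0488 × 45.8 − 1.96) = 61%.

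**3. Information under the written model.** Near HR = 1, an event with the index case and k comparison women at risk contributes k/(k+1)². For k = 4 this is 4/25 = 0.16, the 1:4 benchmark. It falls as comparison women leave, and is zero once the index case has left. Let r be the summed information divided by 0.16 × all events. A nominal 80% at 1:4 becomes Φ(2.8016·√r − 1.96).

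**4. Size of r.** r was found by simulating 1:4 sets with diagnosis dates from Table 1, an administrative end in January 2018 (mean follow-up about 11 years), exponential exits, and the outcome hazard set so that the observed unexposed proportion equals the baseline risk. The exit rates are assumptions.

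| Assumed exits per year | Comparison events uninformative (5 / 20 / 50% risk) | r | Nominal 80% becomes |
|---|---|---|---|
| (a) 0.1%, both groups | 4 / 13 / 30% | 0.99 / 0.96 / 0.87 | 79 / 78 / 74% |
| (b) transfer 5%, no death | 26 / 31 / 40% | 0.89 / 0.86 / 0.78 | 75 / 74 / 70% |
| (c) transfer 5% plus death or recurrence 3% exposed, 1% unexposed | 34 / 38 / 44% | 0.79 / 0.77 / 0.73 | 70 / 69 / 67% |
| (d) transfer 5-8% plus 6% exposed, 2% unexposed | 41-43 / 43-45 / 47-48% | about 0.71 / 0.70 / 0.68 | 65-66 / 65 / 64% |

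Row (a) uses almost nothing beyond the protocol's own inputs: index cases leave mainly at their own outcome, which matters when the outcome is common (sleep disturbances, 50%).

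**5. Separate the two causes in r.** An unstratified Cox model on the same data at 5% risk keeps 80% power in (b), but about 76% in (c) and 73-74% in (d), because exposed women are followed for less time. Stratification alone keeps about 0.89 of the information in (b), 0.87 in (c) and 0.82-0.86 in (d), which corresponds to 72-75% power. In (c), the fall from 80% to 70% is 10 points, of which 4 would occur without stratification.

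**6. Effect on bold cells.** Depression diagnoses, 9%, α 0.01, β 0.20 (printed 1.05, bold against 1.06): 1.057 at 1:4. With r = 0.88 (scenario (b) at 9%), ln HR = 0.0557/√0.88 = 0.0593, so HR = 1.061 and the cell is no longer below 1.06. In the same row, α 0.05, β 0.10 goes from 1.054 at 1:4 to 1.061 with r = 0.79.

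Anxiety diagnoses, 5%, α 0.05, β 0.20: 1.063 at 1:4, 1.071 under (c), about 1.075 under (d).

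**The case against.** The strongest reply is that the size of the loss is not in the documents. Exit rates have to be supplied from outside, and at 5% risk with almost no exits the loss is about one point. That stands, so the range is reported as conditional on assumptions.

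The simulation may also lean towards loss. Matching is within practice, so a practice that stops contributing removes the whole set at once and strands nobody. Table 1 is compatible with this: 13,805/5 = 2,761 diagnoses a year in 2010-2014, against 4,939 over about three years (roughly 1,650 a year) afterwards. Adding an assumed shared practice exit of 5-10% a year to (c) at 5% risk raises power from 70% to about 72-73%. The loss is smaller but does not vanish.

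Three stronger readings are tempting and are not supported.
- A reader might infer that stratification decides the comparison with the published anxiety estimates. It does not: at 5% risk, α 0.05, β 0.20 the minimum HR is already 1.063, above 1.06, from the 1:4 split alone, and it stays below 1.08 under (c) and (d). In the eight primary-outcome rows at α 0.05, β 0.20, an information loss of 10-30% moves no cell across its lowest published value. Across all 32 primary cells at most four move, all at stricter α or β.
- A reader might put the whole shortfall down to stratification. The equal-allocation variance is the larger cause, and part of the rest is shorter exposed follow-up.
- A reader might conclude that the study is underpowered for its primary outcomes, or that matched-set stratification is invalid. At HRs of 1.22, 1.25 (anxiety, 5%) and 1.39 (depression, 3%), power stays at about 100% throughout. The stratified analysis is valid, and no bias is alleged.

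**Conclusion.** The point holds as a correction to stated figures. Table 2 credits every event, whereas the written model discards comparison women's events once the index case has left, so the stated 80% and 90% are not delivered at the printed minimum HRs. This is secondary to the 0.25-for-0.16 variance, which the documents establish without outside assumptions.

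The size of the stratification loss rests on exponential exits at assumed rates (transfer 5-8% a year; death or recurrence 0-6% exposed, 0-2% unexposed), full 1:4 sets and follow-up to January 2018. Sets with fewer than four comparison women, and sets deleted because a comparison woman meets an exclusion criterion, are not in the figures and would lower the information further. The consequence is limited to a few bold cells close to their threshold. The sufficiency sentence survives for HRs of about 1.2 and above, but not without qualification for HRs near 1.06-1.08.

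**What to change.** Recompute Table 2 with the 1:4 split and for the model as written: count only events in sets where the index case and at least one comparison woman are both at risk, each weighted k/(k+1)². Take transfer, death and cancer exit rates from the January 2018 extract already used for the feasibility counts, and state them beside the table. Then restate the minimum HRs, the bold marking and the sufficiency sentence, saying which published effect sizes remain detectable.

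The cost is one rerun of the power calculation on data already held, with somewhat less favourable figures. No extra patients and no change to the main analysis are needed. A sensitivity model stratified on practice, with adjustment for age and calendar period, would keep comparison women's later follow-up. It is an optional preference and not part of this correction.
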